## **MONITORING**

### **Site Monitoring**

The Principal Investigators will manage the study to include site recruitment, collection of essential documents, monitoring, and close out.

### **Data Monitoring and Education**

The patient will be considered to have completed the study, after attaining full, independent oral feedings for two days or after death, discharge, or transfer to a hospital not participating in the study.

Data will be collected using a case report form (Appendix C). Additional study-related documents, study references and information upgrades regarding the project will be available at this site.

If subject is transferred to another hospital following completion of the NTrainer System® intervention, we will have the ability to obtain follow-up data on outcomes.

A representative from KCBioMedix will monitor the progress of the study. The monitor will communicate with each center from the beginning and throughout the study to provide education and weekly review concerning the protocol, electronic randomization, CRF, and data forms for the trial. Monitoring will include 100% review of the primary outcome and secondary outcomes. It will be necessary for the monitor to review those portions of the patients' medical records pertinent to the study.

The monitor will complete clinical monitoring in accordance with Good Clinical Practice Guidelines (GCP).

### **Site Audits and Monitoring**

Facility audit, study initiation audit, midterm audit, and study close-out audits will be conducted during the course of the study by an independent third party.

### **Interim monitoring**

A Data Safety Monitoring Board (DSMB) will be formed for this study which will be an independent advisory board that is comprised of at least one statistician and an expert in the field who are not directly involved in the study. The DSMB will meet once a year or after 50% of the study subjects complete the study whichever comes first. The adverse event reports will be sent to the DSMB as mentioned in the adverse event reporting section. A study report including the subject enrollment, outcomes, adverse events, and protocol violations will be prepared by the study investigators and sent to the DSMB prior to the meetings. The study may be stopped early if definite harm is demonstrated or modified if there is no possibility of answering the research question. The study will not be stopped early for evidence of benefit.

### **Safety Monitoring**

Safety of the study will be monitored by the DSMB. All safety outcomes data will be collected on the case report form and will be reported as adverse events (AE) and serious adverse events (SAE) from each NICU. DSMB will review all the **adverse events** annually and **the** serious adverse events as and when they occur.

### **Expected Adverse Event:**

The anticipated adverse events are any respiratory instability as evidence by Apnea/ Bradycardia or Desaturations during the study intervention NTrainer System® therapy session. This will be submitted to the DSMB annually.

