Infants assigned to the **control group** will receive a sham stimulation program in which the infant will be offered the same type of NICU Soothie® pacifier coupled to the receiver tube and handpiece, but not to the NTrainer System®. Infants assigned to the **control group** will be offered the pacifier by gently placing the pacifier on the lips. The pacifier should not be forced into the mouth and should not be moved in any manner that would represent any form of patterned input such as moving the pacifier in and out, tapping on the lips or face or massaging the mouth or oral facial structure. The sham will be presented **three to four times daily** at the beginning of the first 30 minutes of a tube (gavage) feeding session or 30 minutes before oral feeding. For each session if the baby does not latch onto the pacifier when it is offered, the use of the sham pacifier for that session will be discontinued. However, the infant will remain cradled in a supportive inclined posture for the duration of session. The sham will be used for 10-days distributed over a two week period. All other preparatory, infant positioning and sampling conditions will be equal among groups. The healthcare team will continue to promote feeding and growth as the standard of care for babies in the control group.

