## **Safety**

To help ensure the safety of the study participants, temperature, heart rate, oxygen saturation, and blood pressure will be recorded daily throughout the therapy regimen.

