### **Secondary Outcome Measures**

1. Feeding parameters:
  - a. The time (days) from the initiation of the NTrainer System® training to the first successful and four successful oral feeds in 24 hours.
  - b. Rate of milk transfer (ml/minute) at the time of full oral feeds—no gavage feeding.
2. Development of NNS parameters assessed by the NeoSuckRT® program
  - a. STI – STI NNS Index
  - b. Bursts/Minute
  - c. Events/Burst
  - d. NNS Events/Minute
  - e. % NNN Events
  - f. Total Events/Minute
3. Growth velocity from the initiation of NTrainer System® training to discharge.
  - a. Weight Gain (grams per kilogram per day)
  - b. Head Growth (centimeters per week). Occipitofrontal circumference - place measuring tape around the front of the head, above the brow and the occipital area. The measuring tape should be above the ears.
4. Length of hospital stay (days).
5. Necrotizing enterocolitis, aspiration pneumonia, and death events.
6. Ability to breast feed prior to discharge based on LATCH score.

During the study, adverse events will be monitored to ensure that the rate of reported events does not exceed the expected rate. Also, concomitant medications, concurrent procedures, therapies and protocol deviations will be documented.

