Weight gain (gms/kg/day) and Head Growth (cm/wk) will compared using independent t-tests, provided the data are reasonably normal. If the rates are highly skewed, the Wilcoxon rank sum test will be used.

Binary neonatal morbidity variables such as necrotizing enterocolitis, pneumonia and death will be compared between the two groups using the Cochran Mantel Haenszel (CMH) test, controlling for age group.

The length of hospital stay will be compared between groups using the Wilcoxon rank sum test, since this variable is typically right skewed.

The ability to breast feed prior to discharge (based on LATCH score) is a binary variable, and as such will be analyzed using the Cochran Mantel Haenszel (CMH) test, controlling for age group.

The number of apnea/bradycardia/desaturation free days prior to discharge, and the number of apnea/bradycardia/desaturation with feeds per day after reaching full oral feeds will be summarized descriptively. Statistical analysis of these variables may not be warranted since the decision to discharge may be closely linked to these values, and regardless of treatment group once they reach a certain level the discharge may occur.

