### Flow Diagram for the advancement of oral feeds:

[figure not shown]

**Additional Features of a Successful Feeding** (all criteria must be met):

1. No oxygen desaturation event requiring the new use of or sustained increase (>10% FiO2) in baseline amount of supplemental oxygen.
2. No bradycardic events (heart rate less than 60 beats per min) requiring stimulation and/or multiple bradycardic (>3) events during a 30-minute feeding session (self resolving).
3. Breast feeding events will be considered successful if feeding time is >20 minutes.

If feeding was unsuccessful then the previous days number of oral feeding sessions are to be repeated until success is achieved. The nasogastric tube will remain in place during the oral feeding and any remaining volume of milk not fed in 30 minutes will be gavage fed.

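### Apnoea, bradycardia and desaturation, the one anticipated adverse event, is defined only for NTrainer sessions, so the protocol sets no control-arm rate for the session window in which the risk is named

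*Protocol*

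**What the plan says.** Below, A/B/D stands for apnoea, bradycardia or desaturation.

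- **Definition.** The Expected Adverse Event section gives the anticipated event as "any respiratory instability as evidence by Apnea/ Bradycardia or Desaturations during the study intervention NTrainer System® therapy session". On reporting it adds: "This will be submitted to the DSMB annually".
- **Benchmark.** Secondary Outcome Measures says that "adverse events will be monitored to ensure that the rate of reported events does not exceed the expected rate". No value for that rate appears in the protocol. Interim monitoring says: "The study may be stopped early if definite harm is demonstrated". It does not name the comparison that would show harm.
- **Control sessions.** The control-group text under NTrainerRT Therapy/Intervention schedules the sham three or four times a day for 10 days, as for NTrainer. An infant who does not latch is still held for the whole session. It then states: "All other preparatory, infant positioning and sampling conditions will be equal among groups". Infant Preparation-Positioning keeps every infant on the usual NICU monitors in all sessions.
- **In-session events.** The rule on A/B/D during a session stands under the criteria for exiting an NTrainer therapy. The sham description has no corresponding text.
- **Other A/B/D data.** Data Analysis summarises the number of A/B/D-free days before discharge. It also says that "the number of apnea/bradycardia/desaturation with feeds per day after reaching full oral feeds will be summarized descriptively". The Safety section adds that "temperature, heart rate, oxygen saturation, and blood pressure will be recorded daily throughout the therapy regimen". Appendix B, which applies to both arms, judges each oral feed partly on bradycardia and desaturation; one criterion begins "No oxygen desaturation event requiring the new use of or sustained increase".

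**The concern.** Preterm infants have A/B/D without any device, so a count from NTrainer sessions mixes background with device effect. Only a comparator can separate the two. The trial already has a good one in the sham session, which shares the schedule, positioning and monitoring, but the definition passes over it. With no value for the expected rate either, the protocol cannot answer its own question of whether events exceed expectation.

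The consequences run both ways. The DSMB could take ordinary background for a device signal, or accept a real excess as ordinary prematurity. A smaller gap concerns feeding: A/B/D with feeds is counted only once full oral feeding is reached, so that count leaves out the transition the device is meant to shorten.

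**Working it through.** **1. The plan's own figure.** The number per arm sets the session counts, so I checked it first. Inputs from Sample Size Calculation: difference 5 days, SD 12 days, two-sided alpha 0.05, power 80%.

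- t-test: n = 2 × [12 × (1.960 + 0.842) / 5]² = 90.4 per group.
- Dividing by 0.864, the lower bound of the Wilcoxon test's relative efficiency, gives 104.7, rounded up to 105.

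The stated 105 per group reproduces. The point does not depend on it.

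**2. Sessions inside and outside the definition.**

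- Per infant: 3 × 10 = 30 to 4 × 10 = 40 sessions.
- Per arm: 105 × 30 = 3,150 to 105 × 40 = 4,200 sessions.

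This assumes the full schedule, with no session held or repeated. About as many sham sessions are planned as NTrainer sessions, and the definition covers only the latter.

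**3. Each A/B/D source against what a harm comparison needs.**

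| Source | Available in both arms? | Isolates the session? |
|---|---|---|
| Expected Adverse Event | As worded, NTrainer sessions only | Yes |
| A/B/D-free days before discharge | Yes | No |
| A/B/D with feeds after full oral feeding | Yes | No |
| Daily vital signs | No arm limit stated | No; not event counts, and respiration is not listed |
| Appendix B feed criteria | Yes | No; a feeding-success rule that uses thresholds and omits apnoea |

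No row has yes in both columns. For the second and third rows, the protocol itself warns that the values may be bound up with the decision to discharge in either group, and that formal analysis may not be warranted.

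**4. What one arm alone can and cannot show.** The protocol gives no A/B/D rate, so the proportions here are assumptions. Take as the outcome the proportion of infants with at least one in-session event, which avoids treating repeated sessions in one infant as independent. Suppose 25% of NTrainer infants have an event. If background is 25%, there is no excess. If background is 10%, the excess is 15 percentage points. The one-arm figure is the same in both cases.

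With sham counted alike, n = 105 per arm and two-sided 0.05, power is

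Φ{ [|p₂ − p₁| − 1.96 √(2p̄(1 − p̄)/n)] / √([p₁(1 − p₁) + p₂(1 − p₂)]/n) }.

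For 10% against 25% this is 82%. The NTrainer proportion detectable with 80% power is:

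| Assumed sham proportion | Detectable NTrainer proportion |
|---|---|
| 10% | 24.6% |
| 20% | 37.4% |
| 30% | 48.8% |
| 40% | 59.3% |
| 50% | 68.9% |

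The two-arm comparison would therefore pick up large excesses, of roughly 15 to 19 percentage points over this range. The one-arm count supports no such comparison at any size.

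**The case against.** The strongest reply has four parts.

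- **Control-arm A/B/D data are planned.** A reader might infer that the trial has no control-arm A/B/D rate at all, or that the transition to full feeding has no between-arm A/B/D summary. The documents do not support either. A/B/D-free days before discharge are tied neither to NTrainer sessions nor to the time after full feeding, and the protocol's remark about either treatment group shows that both arms are meant. This stands, and it limits the point to the session window and to the with-feeds count.
- **A list of anticipated events does not define every adverse event.** Safety Monitoring has all safety outcomes entered on the case report form and reported from each NICU, with no arm limit. Appendix C says the forms serve control and experimental patients, and they are not shown. A reader might infer that sham-session events are zero by definition; that goes beyond the text. This also stands.
- **The labels are loose.** The sham is described under the NTrainer intervention heading, and secondary outcomes timed from the start of NTrainer training are compared between arms. The adverse-event wording could be meant to cover sham sessions. That reading is possible, but the sentence names the NTrainer therapy session, and a site has no instruction to read it more widely.
- **A rate and by-arm tables may sit in an SAP or DSMB charter.** That may be so, and their absence here would not be a finding alone. The definition that would feed such tables, however, is fixed in the protocol, and it is one-sided.

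It is also fair to say that Appendix B gives some protection in both arms: a feed with a qualifying event counts as unsuccessful and holds back advancement. It is still not a safety count.

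**Conclusion.** The point holds in a limited form. The protocol defines its one anticipated adverse event for NTrainer sessions only, sets no matching definition for the sham sessions it schedules in parallel, and offers as a benchmark an expected rate without a value. The summaries that do exist in both arms do not isolate the session and are, on the protocol's own account, linked to discharge; the with-feeds count also starts only after the transition.

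The size is 3,150 to 4,200 planned sham sessions left outside the definition, assuming 105 infants per arm and the full schedule. No event rate is available, so neither the number of uncounted events nor the effect on a DSMB decision can be estimated. The conclusion rests on the literal wording and does not show that sites fail to record control events. It does not affect the primary efficacy analysis. It should be corrected, because the safety comparison is weaker than the design allows and the remedy is cheap.

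**What to change.** 1. In Expected Adverse Event, extend the window to *during any NTrainer or sham study session*.
2. Record A/B/D identically for every session in both arms, including sham sessions in which the infant does not latch but is still held. If the case report form already does this, only the protocol wording needs to change.
3. Report the event to the DSMB by arm, with the number of sessions delivered as denominator.
4. In Secondary Outcome Measures, make the concurrent sham rate the comparator in place of the unstated expected rate.
5. Optionally, summarise by arm, from the first oral feed, the feeds that fail the Appendix B bradycardia or desaturation criteria. Label the result as exactly that and not as a full A/B/D count, because those criteria use thresholds and leave out apnoea.

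The cost is protocol wording, possibly one line on the case report form, and slightly more data entry for sham sessions that are already attended and monitored. No clinical rule, sample size or efficacy analysis changes.

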### **Serious Adverse Events**

Death and Stage 3 NEC/ surgical NEC will be considered serious adverse events. This will be reported to the institutional IRB and the study DSMB within 24 hours. The sponsor, KCBioMedix will also be notified as required in their reporting policy.

### **Unexpected adverse events**

Any unexpected serious adverse events that may be life threatening will be reported to the DSMB and the institutional IRB within 10 days of the event occurring.

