### **Treatment Withdrawal Guidelines**

Parents may withdraw their infant from the study at any time. The investigator may withdraw any infant who becomes clinically unstable (e.g., sepsis, stage II or III necrotizing enterocolitis). The healthcare team will then continue the standard of care treatment. Data collection will continue until the infant is discharged from the hospital even after withdrawal to be able to capture any unexpected adverse event related to the study intervention.

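### The safety-reporting rules do not fit together: a non-fatal life-threatening event during a session has no stated prompt route, and unexpected life-threatening events get a slower clock than the listed serious ones

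*Protocol*

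**What the plan says.** The rules stand in consecutive sections under Monitoring in the protocol.

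- **Safety Monitoring.** The DSMB looks at adverse events yearly and at "serious adverse events as and when they occur", with no deadline in days or hours.
- **Expected Adverse Event.** This class is described without a severity limit: "The anticipated adverse events are any respiratory instability as evidence by Apnea/ Bradycardia or Desaturations during the study intervention". The route is: "This will be submitted to the DSMB annually". The IRB is not mentioned.
- **Serious Adverse Events.** Two conditions are named: "Death and Stage 3 NEC/ surgical NEC will be considered serious adverse events". The clock is short: "This will be reported to the institutional IRB and the study DSMB within 24 hours". The sponsor is also told, under its own policy.
- **Unexpected adverse events.** Here a longer clock applies: "Any unexpected serious adverse events that may be life threatening will be reported to the DSMB and the institutional IRB within 10 days". The sponsor is not mentioned.

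Two other places bear on what might count as serious. Secondary Outcome Measures lists "Necrotizing enterocolitis, aspiration pneumonia, and death events". Treatment Withdrawal Guidelines says "The investigator may withdraw any infant who becomes clinically unstable (e.g., sepsis, stage II or III necrotizing enterocolitis").

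**The concern.** Seriousness (how bad the event is) and expectedness (whether it was foreseen) are separate questions. Here they are mixed. One section identifies serious events by naming two of them. Another sorts by expectedness alone and sets no ceiling on severity. A third requires an event to be unexpected, serious and possibly life threatening all at once. An event that is life threatening but foreseen can fall between them.

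The gap lies where it matters most for this device. Respiratory instability during a session is the only harm that the protocol anticipates from the intervention. Interim monitoring allows the study to be stopped early for definite harm, and the text after the secondary outcomes promises to watch that adverse events do not run above the expected rate. Both depend on severe events reaching the DSMB promptly. If the severe form of the named risk travels by the same yearly route as a brief self-resolving desaturation, the DSMB may learn of it late.

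**Working it through.** The protocol states no figure that needs reproducing here. The check is to take each kind of event through the rules as written.

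| Event | On the two-item serious list? | Caught by the unexpected-event rule? | Route that results |
|---|---|---|---|
| Stage 3/surgical NEC | Yes | Not needed | 24 hours to IRB and DSMB |
| Death, not unexpected | Yes | No | 24 hours to IRB and DSMB |
| Death, unexpected | Yes | Yes | Both 24 hours and 10 days |
| Unexpected, life threatening, not listed | No | Yes, if classed as serious; no criterion is given | 10 days to DSMB and IRB |
| Non-fatal life-threatening apnoea in a session | No | No, because it is classed as anticipated | Yearly to the DSMB; no IRB report stated |
| Aspiration pneumonia, stage II NEC, sepsis | No | Only if judged unexpected, serious and possibly life threatening | Otherwise the yearly review of adverse events |

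**The two expedited clocks.** 10 days × 24 hours = 240 hours. 240 / 24 = 10. The limit for an unforeseen life-threatening event is ten times the limit for the two listed events.

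**The in-session event.** The Expected Adverse Event section covers any respiratory instability in a session and sets no severity limit. That removes the event from the unexpected-event rule. It is not on the serious list unless the infant dies or it is accompanied by stage 3/surgical NEC. The yearly submission is the only rule left. The protocol can grade these events: the exit criteria under NTrainerRT Therapy/Intervention single out those that need nursing stimulation or intervention. The reporting rule does not use that distinction.

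**Consistency of the sections.**
1. The unexpected-event rule speaks of serious events in general, so it presupposes more than the two that are named. No section says what the others are.
2. A 10-day allowance fits poorly with DSMB review as events occur.
3. An unexpected death has two different deadlines.
4. The sponsor is named in one expedited rule and not in the other.

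**The case against.** The strongest reply is that the two-item list is not said to be complete. The section states that these events count as serious, not that only these do. The unexpected-event rule implies others, Safety Monitoring has each NICU report both adverse and serious adverse events, and the section on ethical conduct commits the trial to GCP and to federal and state requirements. An investigator could therefore class a life-threatening apnoea as serious. This stands to a point: a reader might infer that such an event certainly goes to yearly review, and the text does not support certainty. But no other criterion is given, and a general commitment to GCP does not override specific clocks that sites will follow.

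Other oversight also exists. Training is held for the infant after an event that needs nursing intervention. The sponsor's monitor is in contact with sites, with weekly review, and checks all primary and secondary outcomes, which include NEC, aspiration pneumonia and death. The DSMB meets yearly, or once half the subjects have finished if that is sooner. These narrow the gap but do not close it. The hold acts on one infant, the monitor's review is not a stated route to the DSMB, and no single event triggers the halfway meeting.

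The mismatch with Safety Monitoring is also softer than a flat contradiction. That section says when the DSMB reviews, while the 10 days is an outer limit for reporting, so a board could review each event as it arrives.

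Three stronger readings are tempting and are not supported:

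- *That the DSMB alone can stop the trial for harm.* Interim monitoring calls it advisory and does not say who decides to stop.
- *That the delay can be turned into a number of infants or courses exposed.* The 10-day limit could be set against the 10 therapy days, or a year against two-week courses. But the therapy days are spread over two weeks, holds and withdrawal intervene, and no enrolment rate is given.
- *That aspiration pneumonia, stage II NEC and sepsis must be serious events.* The protocol treats them as an outcome or as grounds for withdrawal, but nothing in it settles their reporting class.

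**Conclusion.** The point holds as a defect in stated rules, not as missing detail. Two results follow from the wording. A non-fatal life-threatening respiratory event in a session has no stated prompt route to the DSMB or IRB. An unexpected life-threatening event may be reported up to 240 hours after it occurs, against 24 hours for the listed events, with an unexpected death subject to both limits.

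The first result assumes that sites apply the Expected Adverse Event section literally and add no seriousness criterion of their own. If they do add one, practice would be better than the text, but it could differ between sites. The second needs no such assumption about the clocks themselves.

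The consequence is for safety oversight. The primary endpoint, its analysis and the power are not affected. How many events would be delayed cannot be estimated from the protocol.

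**What to change.** Amend the four reporting sections together.

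1. In Serious Adverse Events, define a serious event by its seriousness, including any life-threatening event, whether or not it was expected. Death and stage 3/surgical NEC remain as named examples.
2. In Expected Adverse Event, limit the yearly route to apnoea, bradycardia and desaturation that are not serious.
3. Reconcile Safety Monitoring, Serious Adverse Events and Unexpected adverse events into one expedited route to DSMB, IRB and sponsor, under which unexpected life-threatening events are not reported later than the listed ones. The sponsor has to choose the time limit; the protocol does not settle it.
4. State whether aspiration pneumonia, stage II NEC and sepsis count as serious.

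The cost is a text amendment and a matching change to the adverse-event page of the case report form. No procedures or subjects are added. The downside is more expedited reports, because serious events are common in this population, and the DSMB will have to separate background illness from a device signal.
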